## Abstract

**Background:**

Nurses, the largest workforce in healthcare, are at high risk of depression, anxiety, burnout, and suicidal ideation. Suicide among nurses is higher than the general population. This randomized controlled trial pairs the MINDBODYSTRONG^©^ cognitive-behavioral skills building program with the American Foundation for Suicide Prevention’s (AFSP) Modified Interactive Screening Program (mISP) to reduce depression, suicidal ideation, post-traumatic stress, anxiety, and burnout, and improve healthy lifestyle beliefs, healthy lifestyle behaviors, and job satisfaction in nurses with moderate to high risk of suicide.

**Aims:**

This study aims to determine the effects of the mISP combined with the digitized MINDBODYSTRONG^©^ program versus the mISP alone on depression, suicidal ideation, burnout, anxiety, post-traumatic stress, healthy lifestyle beliefs, healthy lifestyle behaviors, and job satisfaction in 364 U.S. nurses.

**Methods:**

A digitized version of MINDBODYSTRONG^©^ combined with the mISP screening and referral platform will be compared to the AFSP mISP alone through a two-arm randomized controlled trial. Follow-up post-intervention data will be collected at week eight and months three, six, and 12.

**Discussion:**

If successful, this study’s findings could assist nurses who are hesitant to use conventional mental health resources by providing them with confidential aid and learning opportunities to reduce suicidality, depression, anxiety, post-traumatic stress, and burnout and improve healthy lifestyle beliefs, healthy lifestyle behaviors, and job satisfaction.

**Trial/study registration:**

The Ohio State University Protocol Record 2021B0417, Modified Interactive Screening Program Plus MINDBODYSTRONG: A Mental Health Resiliency Intervention for Nurses, is registered and posted at ClinicalTrials.gov Identifier: NCT05582343. First posted date is October 17, 2022.

## Introduction

Suicide remains a leading cause of death in the United States, with non-lethal suicide attempts as high as 10 to 20 times that of completed suicide attempts [1]. Both male and female nurses have a higher death by suicide rate than the general population [2]. The five million plus nurses that make up the largest healthcare workforce in the country report high levels of stress, burnout, and depression [3, 5]. The COVID-19 pandemic exacerbated these experiences and negatively impacted the mental and physical health of nurses [4–7]. A recent study of COVID-19 front-line nurses found that 65% were experiencing burnout [5]. Meanwhile, a systematic review with 16 studies and 18,935 nurses reported the prevalence of burnout via three Maslach Burnout Inventory subscales to be 34.1% emotional exhaustion, 12.6% depersonalization, and 15.2% lack of personal accomplishment [8]. The pandemic’s toll on the nursing profession has resulted in many leaving their jobs or the field entirely, resulting in the great resignation [9–11].

More than 70% of people who die by suicide do not receive needed services within the two months preceding their death [12], and only a small percentage of affected nurses receive needed mental health services [4, 13]. The stigma of seeking help for mental health touches the nursing profession in a significant way. Recent studies have found that nurses are concerned about the way seeking help can affect their employer’s perception of their mental fitness as well as concerns regarding licensure [14]. With 74% of states asking nurses invasive mental health questions on their licensure applications, the stigma continues to be a challenge [15]. Additionally, there is a shortage of mental health providers throughout much of the United States, which makes it difficult to receive timely care for those who pursue services [12].

This innovative study will be the first to assess a novel combination of the American Foundation for Suicide Prevention’s (AFSP) Interactive Screening Program (ISP) with an online digitized adaptation of the well-established manualized cognitive-behavioral skills building (CBSB) intervention, MINDBODYSTRONG^©^ (also known as Creating Opportunities for Personal Empowerment^©^ [COPE^©^]) in the literature), which has demonstrated efficacy in reducing depression, anxiety, and suicidal ideation as well as improving healthy lifestyle behaviors in children, teens, college students and clinicians [16–24].

AFSP’s ISP is a vendor-hosted, anonymous, and widely used mental health screening platform that identifies users with moderate to high risk for suicide and refers them to a therapist who assists in managing their urgent concerns and finding appropriate local resources [25–32]. Participating organizations purchase access to the encrypted, de-identified service and must staff their own mental health specialist to review screening outcomes and communicate with the users. It is endorsed and recognized as an evidence-based suicide prevention intervention and resource by the Council for Graduate Medical Education’s Tools and Resources for Physician Well-Being, American Hospital Association, and U.S. Surgeon General [33]. Use of the ISP has been studied in physicians, medical students, and nurses [25–32], but not in combination with a CBT skills-building program like MINDBODYSTRONG^©^. As done here, the ISP platform can be modified to address resources for specific populations directly; hereafter, it will be referred to as modified ISP (mISP). While AFSP hosts the secure, off-sight server for the screening and communication platform, they have no role in the design, data collection and analysis, decision to publish, or preparation of the manuscript for this protocol and study.

MINDBODYSTRONG^©^ has been adapted for nurses and other healthcare clinicians, with prior RCTs demonstrating significant improvements in participants’ depressive symptoms and job satisfaction [23, 24]. The original version of the program consists of seven manualized sessions that can be delivered by both non-mental health as well as psychiatric mental health professionals, making it more feasible for wide-scale implementation to nurses in healthcare systems across the U.S. Because 55% to 73% of nurses have experienced post-traumatic stress related to the COVID-19 pandemic [9, 34, 35], MINDBODYSTRONG^©^ also includes an optional added module on trauma that participants can choose to complete for a total of eight weekly sessions. Further, for ease of delivery across the nation, MINDBODYSTRONG^©^ has been digitized for this proposed protocol. MINDBODYSTRONG^©^ was selected as the cognitive-behavioral skills building programs of interest as, to our knowledge, other cognitive-behavioral skills building programs were not specifically developed for nurses and have not been tested with them, nor have any other programs been combined with the ISP screen.

Leveraging the strength of both the MINDBODYSTRONG^©^ and mISP could support better identification of suicide risk and offer more actionable support for nurses, potentially lessening mental health stigma and increasing access to confidential mental health care for nurses at risk for suicide.

It is hypothesized that nurses who receive the mISP screening and referral program in combination with the MINDBODYSTRONG^©^ CBSB program will report less depression, SI, post-traumatic stress, anxiety, burnout, and greater increases in personal beliefs, healthy lifestyle behaviors, and job satisfaction immediately post-intervention (8 weeks) as well as at the 3, 6, and 12 month post-intervention follow-up when compared to nurses who receive the mISP screening and referral program alone.

## Materials and methods

### Study aim

This study aims to determine the effects of mISP combined with the digitized MINDBODYSTRONG^©^ versus the mISP alone on depression, suicidal ideation, burnout, anxiety, post-traumatic stress, healthy lifestyle beliefs, healthy lifestyle behaviors, and job satisfaction in U.S. nurses.

### Study design

This study utilizes a two-arm, randomized controlled trial (RCT) design to determine the effects of mISP combined with digitized MINDBODYSTRONG^©^ verses mISP alone. The SPIRIT 2013 Checklist was followed (S1 File), and the approved IRB protocol can be viewed for more detail (S2 File). The mISP and MINDBODYSTRONG^©^ are carried out individually by the participant. Nurses identified with moderate to high risk of suicide through the mISP will be randomly assigned to MINDBODYSTRONG^©^ or the attention control group (i.e., mISP alone). Depression, suicidal ideation, burnout, anxiety, post-traumatic stress, healthy lifestyle beliefs, healthy lifestyle behaviors, and job satisfaction in U.S. nurses will be assessed to determine effectiveness. The post-intervention follow-up will occur at 8 weeks, 3, 6, and 12 months. These touchpoints for follow-up were selected to assess the sustainability of the intervention’s effect over time, determine whether a booster session would be needed during the first year, and identify what month would be most appropriate to do so.

Data will be collected on two platforms: (1) the mISP and (2) REDCap–a browser-based software specifically designed for clinical and translational research. Two platforms for data collection are required as the mISP is limited in its ability to link data overtime due to the encryption. To maintain data fidelity, an additional baseline survey will be completed by the participants in REDCap after completing the initial mISP screening, and all follow-up surveys will be taken in REDcap to allow for data linking at each point for analysis. Randomization will occur via REDCap. The schedule for enrollment, interventions, and assessments are viewable in Fig 1.

**Fig 1 pone.0303425.g001:**
[figure not shown]
Schedule of enrollment, interventions, and assessments for mISP plus MINDBODYSTRONG^©^. Timepoints: -t0: Data collected after consent to determine eligibility, t1: baseline data collected at time of allocation, t1: 8 weeks (immediately post-intervention), t2: 3 months, t3: 6 months, t4: 12 months. mISP = Modified Interactive Screening Program; GAD-7 = Generalized Anxiety Disorder-7; PHQ-9 = Patient Health Questionnaire-9; PC-PTSD-5 = Primary Care Post Traumatic Stress Disorder Screen for Diagnostic and Statistical Manual of Mental Disorders-5; and SRRS = Social Readjustment Rating Scale. Specific Outcome variables from AIMs: depression, suicidal ideation, burnout, anxiety, post-traumatic stress, healthy lifestyle beliefs, healthy lifestyle behaviors, and job satisfaction.

### Sample size and power analysis

A power analysis was conducted based on two-sample t-tests to compare pre- vs. postintervention means with two-tailed tests and a study-wide type I error rate of 5% to adjust for multiple comparisons from seven outcomes and four between-group pre-post comparisons per outcome. Given previous positive results with MINDBODYSTRONG©, yielding a large effect size of .98 requires a sample size of 30 (21 after accounting for 30% attrition), which would detect effects with 80%. However, given the untested nature of the electronic on-line version of MINDBODYSTRONG©, a medium effect of .5 was used to calculate a desired sample of 254, which would detect intervention effects on outcomes (depression, SI, burnout, anxiety, post-traumatic stress, healthy lifestyle beliefs, healthy lifestyle behaviors, and job satisfaction) with 80% power and study-wide type I error rate of 5%. With an expected 30% attrition, we will need a target recruitment of at least 364 nurses from the ANA to ensure an analytical sample size of 254.

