### Data analysis

We will conduct intent-to-treat analyses. Descriptive statistics will be first used to examine variable distribution, identify any data abnormality such as outliers, and summarize sample characteristics, stratified by intervention and control groups. Appropriate data transformation will be performed if needed to achieve normality. For each outcome variable, mixed-effects linear regression modeling will be used to fit the outcome as a linear function of intervention, time, intervention dose, and their interactions. Generalized linear mixed-effects regression with appropriate link function will be used if data fail the normality assumption. From the model, we will obtain estimates on the between-group difference in the change of outcome measure from baseline at each follow-up time point and estimates on the dose effect of the completed sessions in the MINDBODYSTRONG^©^ program. The model will be further extended to adjust for covariates, examine nonlinear relationships, and explore the heterogeneity of intervention effects across subgroups.

The study has seven outcomes and four between-group comparisons of pre-post changes for each outcome. Therefore, multiple testing adjustment to keep the study-wide type I error rate under 0.05 will be employed. Missing data due to attrition at longitudinal follow-up is expected. We will examine the extent and pattern of missing data, and perform appropriate multiple imputation according to missing data mechanism. The mixed-effects regression modeling allows for missing at random. This analysis will be repeated with and without multiple imputation. If missing not at random exists, pattern mixture modeling will be used instead. Sensitivity analysis will be used to examine the robustness of study findings before vs. after multiple imputation or under pattern-mixture modeling. We will use SAS 9.4 for all quantitative analysis. We will conduct two-sided tests and use Bonferroni adjusted p-values < 0.007 for statistical significance to keep the study-vide type I error rate under 0.05. Due to the conservative nature of Bonferroni adjustment for multiple testing, we will conduct sensitivity analysis using other approaches (e.g., Hommel method) [52]. Regardless of statistical significance, we will report point estimates, their precision (e.g., 95% confidence intervals), and effect sizes.

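### The stated sample size for an effect of 0.98 (30 recruited, 21 analysed) does not give 80% power under the paragraph's own method, which needs about 66 to 72 analysed

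*Protocol article*

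**What the plan says.** The Sample size and power analysis section of the protocol article sets out one method for the whole paragraph. The calculation is "based on two-sample t-tests to compare pre- vs. postintervention means with two-tailed tests and a study-wide type I error rate of 5" per cent, and the multiplicity to be covered is "seven outcomes and four between-group pre-post comparisons per outcome".

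Two scenarios follow.

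- **Effect of 0.98, from earlier work with the programme:** "a large effect size of .98 requires a sample size of 30 (21 after accounting for 30% attrition), which would detect effects with 80" per cent, which can only mean power.
- **Effect of 0.5, adopted because the online version is untested:** 254 analysed for 80% power at a study-wide 5%, and at least 364 recruited to allow for 30% attrition.

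The sentence that gives 254 names eight outcomes, not seven. The Data analysis section again counts seven outcomes with four comparisons each, but says the analysis will "use Bonferroni adjusted p-values < 0.007 for statistical significance".

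**The concern.** Required sample size for a two-sample comparison varies with the inverse square of the effect. If 254 is right for 0.5, the figure for 0.98 should be about a quarter of it, not a twelfth (254/21 = 12.1). So the two scenarios cannot come from the same calculation, although the paragraph presents them under one method.

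What is at stake is the accuracy of the published justification. A reader is told that the earlier effect could be detected with 21 analysed participants, which overstates the margin built into the trial. The paragraph also leaves two other things open that determine the power of 254: how many outcomes are tested, and at what alpha each test is done.

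**Working it through.** **Inputs.** Two-sample t-test, two-sided, study-wide 5%, 7 × 4 = 28 comparisons, effects of 0.98 and 0.5, power 80%, attrition 30% (all from Sample size and power analysis); 1:1 allocation (Randomization); threshold 0.007 and the Bonferroni method (Data analysis). The per-test level of 0.05/28 = 0.00179 is not printed. It is inferred from the 28 comparisons and the Bonferroni method, and step 1 tests it.

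**Formulas.** Normal approximation: n per arm = 2(z₁₋α/₂ + z₀.₈)²/d². Exact: power of the two-sample t-test from the noncentral t with 2n − 2 degrees of freedom and noncentrality d√(n/2). Recruitment = analysed/(1 − 0.30).

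**Step 1: reproduce 254 for d = 0.5.** At 0.05/28, z₁₋α/₂ = 3.124 and z₀.₈ = 0.842.

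- Normal: 2 × (3.966)²/0.25 = 125.8, so 126 per arm, 252 in total.
- Exact t: 129 per arm, 258 in total.
- 127 per arm (254) gives 80.5% (normal) or 79.4% (exact t).
- 254/0.7 = 362.9, so 363, or 364 for equal arms of 182.

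The operative figures reproduce closely, which supports 0.05/28 as the level used.

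**Step 2: same method, d = 0.98.**

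- Normal: 2 × (3.966)²/0.9604 = 32.7, so 33 per arm, 66 in total. Scaling the protocol's own figure agrees: 254 × (0.5/0.98)² = 66.1.
- Exact t: 36 per arm, 72 in total (power 81.3%).
- Recruitment: 66/0.7 = 94.3, so 95; 72/0.7 = 102.9, so 103 (104 for equal arms).
- At 0.007, exact t: 28 per arm, 56 in total; 56/0.7 = 80 recruited. The normal approximation gives 27 per arm, 54 in total.

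**Step 3: power of the stated figures at d = 0.98** (exact t, two-sided).

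| Analysed | 0.05/28 | 0.007 | 0.05, unadjusted |
|---|---|---|---|
| 21 in total | 12.4% | 25.3% | 56.7% |
| 30 in total | 25.2% | 42.6% | 73.6% |
| 21 per arm | 44.4% | 63.1% | 87.3% |
| 30 per arm | 69.6% | 83.6% | 96.2% |

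The stated attrition step is consistent in itself (30 × 0.7 = 21); the fault lies in the starting figure. No two-sided two-sample test with 21 or 30 in total reaches 80%, even unadjusted, where the need is 36.

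**Step 4: possible source.** A one-group paired t-test at 0.05/28 and d = 0.98 needs n = 21.2, and n = 21 gives 79.2%. That is close to the stated 21.

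**Step 5: what 254 gives at d = 0.5 under each candidate alpha** (exact t, 127 per arm).

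- 0.05/28 (seven outcomes × four comparisons): 79.4%.
- 0.05/32 (eight outcomes × four comparisons): 78.3%.
- 0.007 (close to 0.05/7 = 0.00714, so a division by seven outcomes alone): 89.6%.

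**The case against.** The strongest reply is that the 0.98 scenario decides nothing. The next sentence sets it aside, and 254, 364 and 182 per arm all rest on 0.5. This stands, and it limits the point to a correction of the text. The qualitative message also survives: 254 is still about 3.5 times 72 (254/72) and 3.8 times 66.

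A second reply is that some readings of 21 or 30 do reach 80%. They include 21 per arm with no multiplicity adjustment (87.3%), 30 analysed in total with an unadjusted one-sided 5% test (83.5%), and 30 analysed per arm at 0.007 (83.6%). Each departs from the text: the first two drop the stated adjustment, the second also drops the two-tailed test, and the third takes 30 as analysed per arm, although the text reduces 30 to 21 for attrition.

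A third reply is that no single replacement figure follows from the document. This also stands. The answer is 66 or 72 at 0.05/28 depending on the formula, and 56 at 0.007 by exact t. The exact t-test would ask for 258, not 254, at d = 0.5, so 72 has no special claim over 66.

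**Conclusion.** The statement that an effect of 0.98 needs 30 recruited and 21 analysed for 80% power is wrong under the method the paragraph states. The need is about 66 to 72 analysed (95 to 103 recruited) at 0.05/28, or 56 (80 recruited) at 0.007. With 21 in total, power is about 12% and 25% respectively. This assumes equal arms, Bonferroni division, and 0.98 used as a standardised between-arm difference in the way 0.5 is used to reach 254.

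Several stronger conclusions might be inferred, and the document does not support them.

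- **That the trial is too small.** The target of 364 rests on 0.5, and that calculation reproduces.
- **That a paired test was used by mistake.** The near-match is suggestive, and the phrase "A power analysis was conducted based on two-sample t-tests to compare pre- vs. postintervention means with two-tailed tests" leaves room for confusing a before-after test with a between-arm one. But the document does not say how 21 was obtained, and a paired test needs 22 in whole participants.
- **That 0.05/32 is the correct level and 254 therefore gives 78%.** Two sections count seven outcomes. The list in the sample size paragraph has eight, while the list that opens the Discussion has seven, without post-traumatic stress. The stated threshold of 0.007 would instead give about 90%. Only the authors can settle the count and the level.
- **That a later study would be planned on 30.** Nothing in the document proposes this, and the paragraph itself declines to rely on 0.98.

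The importance is minor: a checkable error in a background scenario, next to an unresolved count and alpha that do affect the stated power of 254.

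**What to change.** - Delete the 0.98 scenario, or replace its figures with ones derived by the same formula and alpha as 254, stating both.
- Name the test as a two-sample comparison between arms of change from baseline.
- Settle whether seven or eight outcomes are tested, and use the same count in Sample size and power analysis, Data analysis and the Discussion.
- Settle one per-test alpha. The 28 comparisons in the sample size paragraph imply 0.05/28, while Data analysis states 0.007.
- Restate the power of 254 at d = 0.5 for the alpha chosen: about 79% at 0.05/28, 78% at 0.05/32, or 90% at 0.007.

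The cost is a text correction and a decision on the outcome count and alpha, best made before outcome data are examined. Enrolment does not change.

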### Sample and setting

The sample will primarily be nurse members of Healthy Nurse Healthy Nation (HNHN), a healthy lifestyle program through the American Nurses Association Enterprise (ANA). Healthy Nurse, Healthy Nation is a free online program designed for nurses to support six domains of wellbeing, including mental health. A membership with the ANA is not needed to join HNHN. The minimum sample size is 364 with 182 participants per arm. To reach this sample size, a random sample of 5,200 nurses is anticipated.

HNHN will disseminate recruitment information via email regarding the opportunity to participate in the study. If the minimal sample size is not obtained via HNHN recruitment efforts, additional professional nursing organizations and health systems will be accessed, and the study team will use convenience sampling with the snowball method or social media advertising (if necessary). HNHN recruitment emails, using a random sample, offer a direct link to the consent form (S3 File). For participants in the convenience sample (non-HNHN recruitment source), a delayed recruitment method will be utilized to manage the flow of participants. The delayed recruitment will collect email addresses of potential participants in REDCap. Nurses will receive an acknowledgement of providing their contact information by email. As available and appropriate, email invitations to consent form will be sent to potential participants via email. If study is no longer accepting participants, nurses will be notified via email and provided with mental health resources.

Nurses who consent to participate in the study will be screened for participation through the mISP. Eligible participants who provide consent will be called by a study team member to ensure that any questions about the study are answered. Inclusion criteria for participation is currently working as a nurse with a license to practice and being identified by the mISP as having moderate to high risk of suicide (i.e., mISP designated Tier 1 or Tier 2). Nurses identified as having minimal to no distress (i.e., mISP designated Tier 3) are excluded, as are nurses who have previously participated in the MINDBODYSTRONG program. Table 1 describes how the mISP determines tier designation and level of distress.

**Table 1 pone.0303425.t001:** Determining mISP tier designation and level of distress.

	Level of Distress
